### Assessments

At baseline a survey is administered by research staff immediately after informed consent is obtained. At 1, 3, and 6 months after hospital discharge, research staff contact participants by telephone to conduct follow-up surveys. Participants who report being continuously abstinent from tobacco for 6 months are re-contacted at 12 months.

Prior to each follow-up call, participants are sent a postcard reminding them that research staff will be contacting them in the near future. The research staff makes up to 15 call attempts, calling at different times and on different days, making more attempts during the participants’ self-reported preferred call time. After an 8^th^ unsuccessful call attempt, the research staff calls the participants’ alternate contacts, people whom the participants specified would know how to reach them, to verify the participants’ contact information. Mailed surveys with a stamped return envelope are sent upon reaching the 8^th^ and 15^th^ unsuccessful call attempts. Upon reaching a 10^th^ unsuccessful call attempt, the participant receives a text message requesting a call to the study hotline. Participants are compensated $20 for completing each follow-up survey.

At the 6 month follow-up, a participant’s self-report of past 7-day tobacco abstinence is biochemically confirmed. The participant is asked to mail a saliva sample for assay of cotinine, a nicotine metabolite with a 16-hour half-life [29]. Because this test is falsely positive for participants using NRT or electronic cigarettes (e-cigarettes), we request that individuals using either of these visit the hospital for an expired air carbon monoxide (CO) test. Participants receive $50 dollars for returning the cotinine kit or completing a CO test, regardless of the result obtained. Because smoking status can change between self-report and the time of saliva collection, we reassess participants’ use of any form of nicotine in the 7 days prior to the date of saliva collection or CO test. This includes use of any tobacco products, e-cigarettes, and nicotine replacement products.

## Measures

### Participant surveys

The survey instruments cover the following domains (Table 3).

**Table 3 Tab3:** **Helping HAND trial measures and schedule of administration**

	**Baseline**	**Outcomes**			
**Measure**		**1 Month**	**3 Month**	**6 Month**	**12 Month**
Demographic factors					
Age, sex, race/ethnicity, educational attainment, employment status, martial/partner status, type of housing	X				
Smoking history					
Number of cigarettes per day, use of other tobacco products, use of electronic-cigarette, number of years smoking, prior quit attempt, smoker in household, home smoking policy	X				
Nicotine dependence (time to first cigarette)	X				
***Previous cessation medication use***	***X***				
Importance in ability to quit	X				
Confidence in ability to quit/stay quit	***X***	X	***X***	***X***	
Tobacco abstinence status–self-report					
Cigarette smoking status	X	X	X	X	***X*** ^1^
Non-cigarette tobacco use status	X	X	X	X	***X*** ^1^
Electronic-cigarette use	X	X	X	X	***X*** ^1^
Tobacco abstinence status–biochemical validation					
Saliva cotinine or expired aired CO				X	
Quit attempt (>24 hours)	X	X			
Hospital admission or emergency room visit		X	X	X	
***Quality of life (EQ-5D)***	***X***			***X***	
***Anxiety and depression symptoms (PHQ-4)***	***X***	***X***	***X***	***X***	
Alcohol use (AUDIT-C)	X			***X***	
***Other non-tobacco substance use***	***X***				
Satisfaction with IVR		X	***X***		
***Satisfaction with Quit Coach***		***X***	***X***		
Smoking during index hospital stay		X			
Smoking cessation medication used after discharge		X	X	X	
Smoking cessation counseling used after discharge		X	X	X	
***Other smoking cessation programs/resources used***		***X***	***X***	***X***	

***Items in bold italics were only in Helping HAND 2.***

All other measures were used in both Helping HAND 1 and 2.

^1^Asked only of participants who self reported continuous abstinence at 6 month follow-up.

*Demographic factors*: sex, age, race/ethnicity, educational attainment, employment status, marital/partner status, and type of housing are collected by participant interview and chart review at baseline.

*Tobacco use history* includes cigarettes per day, use of other tobacco products, and use of electronic cigarettes in the month prior to admission, number of years smoking, prior quit attempt (yes/no), presence of a smoker in the household, and home smoking policy. *Prior tobacco treatment* is assessed at baseline by asking about previous use of NRT, bupropion, varenicline, telephone counseling support, and in-person counseling support. *Nicotine dependence* is assessed by asking time to first cigarette of the day.

*Intention to quit* upon discharge is assessed with the item described in Table 2. Perceived *importance* of quitting and perceived *confidence* in ability to quit are assessed with 5-point Likert-type scales ranging from “not at all” to “very” at baseline. Confidence is reassessed at each follow-up.

*Alcohol use* in the past year is assessed at baseline and 6 months using the three-item Alcohol Use Disorder Identification Test—Consumption [30]. *Other substance use* is assessed at baseline by asking about any use in the past year of marijuana, cocaine, crack, stimulants, and opioids. Injection drug use is assessed by asking about participants’ lifetime use and their use within the past year.

*Anxiety and depression symptoms* are assessed at baseline and at each follow-up using the Patient Health Quessionaire-4, a 4-item inventory rated on a 4-point Likert scale ranging from “not at all” to “nearly every day” [31]. The first two questions measure anxiety symptoms and the latter two measure depression symptoms. Scores range from 0-12, with higher scores indicating more symptoms.

*Quality of life* is measured at baseline and 6-month follow-up using the EQ-5D instrument [32]. It assesses quality of life on a 5-point Likert scale with answers ranging from “no problems” to “unable” and “not at all” to “extremely”. The questions range from physical mobility (problems walking, washing, dressing, pain, and discomfort) to psychological (feeling anxious or depressed).

#### Inpatient experience with tobacco abstinence

At 1-month follow-up, participants rate the difficulty they had maintaining abstinence in the hospital by answering the question, “How hard was it not to smoke while you were in the hospital?” (4-point Likert-type scale, “not at all” to “very”). Participants are asked whether they used any FDA-approved smoking cessation medications in the hospital. Cigarette use and electronic cigarette use while in the hospital are assessed by asking, “Did you smoke a cigarette (or an electronic cigarette), even a puff, during your stay in the hospital?” Participants who report using either product are asked, “Did you smoke inside the hospital building, outside, or both?”

### Hospital record review

We obtain health insurance, hospital length of stay, primary and secondary hospital discharge diagnoses, hospital service, and participants’ disposition after discharge (home or rehabilitation facility) from hospital records. Chart review at baseline is done to obtain height, weight, and history of co-morbid medical diagnoses; these include hypertension, diabetes, dyslipidemia, myocardial infarction or coronary heart disease, stroke, cancer (other than skin), and emphysema or chronic bronchitis.

### Outcome measures

#### Tobacco abstinence

The primary smoking outcome is a biochemically-validated 7-day point prevalence abstinence from all tobacco products at 6 months after discharge. This is determined by responses to these questions: “In the past 7 days have you smoked a cigarette, even a puff?” and “In the past 7 days, have you used any tobacco products other than cigarettes such as cigars, pipes, snus, or chew?” Participants are considered to be smokers for the primary outcome if they are lost to follow-up or report tobacco abstinence but do not provide a biochemical sample that meets criteria for abstinence (saliva cotinine ≤10 ng/ml or expired air CO ≤9 ppm).

Secondary outcome measures of tobacco abstinence status include the following: (1) self-reported 7-day point prevalence tobacco abstinence at 1, 3, and 6 months; (2) self-reported sustained 7-day abstinence from cigarettes and other tobacco products at 1, 3, and 6 months; (3), self-reported continuous abstinence from cigarettes and other tobacco products at 1, 3, 6, and 12 months (‘Since you left the hospital, have you smoked a cigarette, even a puff? Have you used any other tobacco products such as cigars, pipes, snus, or chew?)’; (4) duration of tobacco abstinence after discharge (How soon after you left the hospital, did you smoke your first cigarette, even a puff?); and (5) proportion of participants who make a 24-hour quit attempt after discharge (‘Since you left the hospital have you not smoked for 24 hours because you were trying to quit?’).

Whether to classify e-cigarette users as tobacco abstinent or not is under discussion by tobacco researchers. No clear criteria have yet been adopted. For this study, we consider e-cigarette use to be comparable to long-term NRT use. Individuals who report abstinence to all conventional tobacco products but are using e-cigarettes and meet criteria for biochemical validation of abstinence by expired air CO are considered to be tobacco abstinent. A sensitivity analysis will be done to determine how tobacco abstinence rates change when e-cigarettes only users are classified as tobacco users.

#### Smoking cessation treatment use and adherence

We hypothesize that the intervention is mediated by increasing participants’ use of evidence-based pharmacotherapy and counseling after discharge. Participants report on the extent of any use of either modality at each outcome assessment. Smoking cessation counseling is defined as telephone or in-person counseling from any source including a physician. Pharmacotherapy includes use of NRT (nicotine patch, gum, lozenge, inhaler, or nasal spray), bupropion, or varenicline. For medications used, we assess dose, starting date of use, frequency and duration of use, reason for termination, and whether the patient changed their dosage due to side effects.

The principal measure of treatment use is the use of any pharmacotherapy or counseling after discharge; we will also calculate the proportion of participants who use pharmacotherapy and counseling separately. Outcome measures for pharmacotherapy include any use and duration of use. Outcome measures for counseling include any use and number of contacts.

#### Health care utilization

We will calculate the rate of all-cause re-hospitalizations, re-hospitalization for coronary heart disease, emergency room visits, and all-cause deaths over 6 months after the index hospitalization. Measures include (1) number of hospital readmissions, (2) length of stay in hospital, (3) number of emergency room visits, and (4) total number of hospitalizations and emergency room visits. An electronic health record tracking system automatically notifies research staff when a study participant has an emergency room visit or hospitalization at facilities in Partners Healthcare System, the integrated health care delivery system to which MGH and NSMC belong. At the end of the study, data on these events will be obtained from Partners billing data. At UPMC, information about hospital readmissions to UPMC-affiliated hospitals is obtained from chart review of participants’ electronic health records.

Information about hospitalizations and emergency room visits outside UPMC and Partner’s Healthcare System are obtained from participant surveys, by asking the questions “Since you were discharged from [hospital name] on [date] have you gone to the emergency room or stayed overnight at any hospital? This includes rehabilitation or skilled nursing facilities”. We request hospital name, type of visit (either ED, admission, inpatient rehab,) length of stay, and the hospitalization date. This is supplemented by requesting medical records of admissions to hospitals outside Partners HealthCare System and UPMC-affiliates.

#### Program satisfaction

Participants in the Sustained Care arm are asked about their satisfaction with the telephone counseling by the Quit Coaches and the automated IVR calls. Participants who ever spoke to a Quit Coach are asked: (1) “How helpful was the Quit Coach?” (“not at all” to “very”); (2) “If a friend or family member who smokes and wanted to stop were hospitalized, would you recommend that they speak with a Quit Coach to help them stop smoking?” (“strongly recommend” to “strongly not recommend”); and (3) an open-ended question, “What, if anything, was helpful or not helpful about the Quit Coach program?” Those who received at least one IVR call are asked parallel questions regarding the automated telephone system, using the same scales. Additionally we ask, “How helpful was it to have the automated telephone calls refill your stop smoking medication for you?” (“not at all” to “very”).

### Quality assurance

Multiple actions are taken to ensure the consistency of TTS services, recruitment, and enrollment across all three sites. These included creating standardized protocols across sites for counseling, referring, and enrolling patients. All counselors and recruiters were trained together prior to recruitment, specifically focusing on inclusion and exclusion criteria. Regular meetings of certified TTS counselors from all sites are held to ensure that the same standardized protocol is followed for referrals. Follow-up assessments were centralized at one study site.

### Data analysis

A total sample of 1350 was planned to detect a difference of 4.8% (12.8% vs. 8.0%) in the primary outcome measure, validated 7-day tobacco abstinence at 6-month follow-up, with 80% power and a 2-tailed type I error rate of .05. Analysis of study data will use an intention-to-treat approach. In the primary analysis, subjects lost to follow-up due to all circumstances will be coded as smokers for smoking status outcomes. A sensitivity analysis will be conducted based on different assumptions on missing data [33]. Multiple imputation techniques will also be used to take into account uncertainty due to missing data.

#### Primary outcome

The primary smoking outcome is biochemically-validated 7-day point prevalence abstinence from all tobacco products at 6 month follow-up. For the analysis, Cochran-Mantel-Haenzel tests will first be used to determine whether intervention effects are consistent across the 3 study sites. Logistic regression analyses will be used to compare the effect of study arm on the primary outcome measure, adjusting for study site.

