**Methods/Design:**

A 2-arm, 3-site randomized controlled trial is testing the hypothesis that a multi-component Sustained Care intervention is more effective than Standard Care in helping hospitalized cigarette smokers stop smoking after hospital discharge. The trial enrolls adult daily cigarette smokers who are admitted to 1 of 3 participating hospitals in Massachusetts or Pennsylvania. Participants receive the same smoking cessation intervention in the hospital. They are randomly assigned to receive either Standard Care or Sustained Care after hospital discharge. Participants in the Sustained Care arm receive a free 3-month supply of FDA-approved smoking cessation medication and 5 interactive voice response calls that provide tailored motivational messages, medication refills, and access to a live tobacco treatment counselor. Participants in the Standard Care arm receive a smoking cessation medication recommendation and information about community resources. Outcomes are assessed at 1, 3, and 6 months after discharge. The primary outcome is biochemically-validated tobacco abstinence for the past 7 days at 6-month follow-up. Other outcome measures include self-reported tobacco abstinence measures, use of medication and counseling after discharge, hospital readmissions, and program cost-effectiveness.

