We tested the effectiveness of our post-discharge tobacco treatment model in the Helping Hospital-initiated Assistance for Nicotine Dependence study (Helping HAND 1), a randomized controlled trial of 397 smokers admitted to one large Boston, MA, hospital. Smokers who received smoking cessation counseling in the hospital and planned to quit smoking after discharge were randomly assigned to the Sustained Care intervention, which provided free medication and IVR follow-up for 3 months, or to Standard Care. Smokers assigned to Sustained Care were more likely to use smoking cessation therapy (both pharmacotherapy and counseling) after hospital discharge and were more likely to achieve the primary outcome measure, biochemically-validated past 7-day tobacco abstinence at 6 month follow-up (26% vs. 15%; RR 1.71, 95% CI, 1.14-2.56) [22].

The current study, Helping HAND 2 (HH2), builds on the Helping HAND 1 (HH1) trial in several ways that aim to test the intervention’s potential when applied to a more diverse patient population and setting (Table 1). To determine whether the HH1 study findings apply to a more diverse population, we broadened study inclusion criteria to include smokers with alcohol and other substance abuse. Although they have a high prevalence of smoking [23], these individuals had been excluded from the HH1 trial because of concern about medical or psychiatric instability. We also prioritized the recruitment of smokers with HIV infection, who also have a high smoking prevalence [24]. Furthermore, we expanded the program from one to three hospitals located in two states and included both academic and community hospitals. Additionally, we streamlined the intervention in order to facilitate its adoption into actual clinical practice. To access a live counselor, participants in the HH1 study used the IVR system to request a separate call back from the hospital counselor at a later time. In contrast, in the HH2 trial, when participants indicate the desire to speak with a counselor during an IVR call, they are immediately transferred during that call to a telephone counseling service. That service is identical to a telephone quitline, a community-based smoking cessation resource that is available free to every U.S. smoker at www.smokefree.gov. Finally, to demonstrate the stability of tobacco abstinence, we extended follow-up to 12-months to assess smoking status of participants who reported uninterrupted abstinence at 6 months after discharge.

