### Assignment to treatment group

At each study site participants are randomly assigned to either Standard Care or Sustained Care by research staff in a 1:1 fashion using permuted blocks of 8. Randomization is stratified into five groups: four strata were created by crossing daily cigarette consumption (<10 versus ≥10 cigarettes per day) with admitting service (cardiac vs. non cardiac), and a fifth stratum was created for HIV-infected patients. A series of sealed manila envelopes was created for each stratum, with the randomization ID on the outside of the envelope and the study arm assignment inside the envelope. The research assistant informs the participant and initiates the protocol for the assigned study arm. The study is not blinded to participants or to research staff, but enrollment and follow up activities are conducted by research staff members not involved with recruitment.

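### The test named to check that effects are consistent across sites (Cochran-Mantel-Haenszel) tests for a zero common effect, so it cannot assess consistency and can mislead in either direction

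*Protocol article*

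**What the plan says.** In the Data analysis section, under Primary outcome, the article describes two steps. The first is that "Cochran-Mantel-Haenzel tests will first be used to determine whether intervention effects are consistent across the 3 study sites". The second is that "Logistic regression analyses will be used to compare the effect of study arm on the primary outcome measure, adjusting for study site". It names no homogeneity test and no arm-by-site interaction anywhere, and it does not say how a significant or non-significant result of the first step would be read or acted on.

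The design is three sites with randomisation within site: "At each study site participants are randomly assigned to either Standard Care or Sustained Care by research staff in a 1:1 fashion". The sample size statement reads "A total sample of 1350 was planned to detect a difference of 4.8% (12.8% vs. 8.0%) in the primary outcome measure", "with 80% power and a 2-tailed type I error rate of .05". In the primary analysis, "subjects lost to follow-up due to all circumstances will be coded as smokers for smoking status outcomes".

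The Background lists the extension to more sites among the ways this trial builds on its predecessor: "we expanded the program from one to three hospitals located in two states and included both academic and community hospitals". Table 1 gives generalizability as the goal of that change.

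**The concern.** The named test and its stated purpose do not match. The CMH null hypothesis is that the odds ratio common to all sites equals 1. Consistency across sites means that the site odds ratios equal one another, whatever their value. The two hypotheses can be true or false independently:

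- A uniform benefit makes CMH significant although the sites agree perfectly.
- Effects in opposite directions can cancel and leave CMH non-significant although the sites disagree.

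The second step does not fill the gap. A logistic model adjusted for site, without an interaction term, assumes one common arm effect. It asks nearly the same question as CMH, so the first step in effect repeats the primary test.

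At stake is what the report can say about carrying a single-hospital result over to three hospitals of different types. The only check of that named in the article gives no information on it.

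**Working it through.** **Inputs.** From the article: 1,350 participants in total, 12.8% versus 8.0%, 80% power, two-sided 0.05, 1:1 allocation within site, three sites, losses coded as smokers. Assumed: 225 per arm at each site (1,350 / 6), because no split is given; an unequal split of 340/110/225 per arm was also tried. All heterogeneity patterns below are assumptions.

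**Step 1: reproduce the plan's own figure.** The mean rate is (0.128 + 0.080)/2 = 0.104.

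n = [1.96·√(2·0.104·0.896) + 0.8416·√(0.128·0.872 + 0.080·0.920)]² / 0.048² = (0.8461 + 0.3622)² / 0.002304 = 633.7

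With the continuity correction, n′ = (633.7/4)·[1 + √(1 + 4/(633.7·0.048))]² = 674.7, that is 675 per arm and 1,350 in total. This matches exactly, so the design figures are sound.

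**Step 2: worked examples.** With 225 per arm in a site and m quitters there in total, each site contributes m/2 expected Sustained Care quitters and variance V = m(450 − m)/(4·449). Then CMH = (Σ observed − Σ expected)² / ΣV on 1 df.

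- *Identical sites*, Sustained/Standard quitters 29/18 at all three (odds ratio 1.70 each). Observed 87, expected 70.5, ΣV = 3·(47·403/1796) = 31.64. CMH = 16.5²/31.64 = 8.60, p = 0.003. Breslow-Day homogeneity test: p = 1.0.
- *Opposing sites*, 36/22, 22/22 and 9/22 (odds ratios 1.76, 1.00, 0.38). Observed 67, expected 66.5, ΣV = 12.66 + 9.95 + 7.23 = 29.84. CMH = 0.5²/29.84 = 0.008, p = 0.93. Breslow-Day: p = 0.008.

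In each case the CMH result points the wrong way if it is read as a verdict on consistency.

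**Step 3: long-run behaviour.** Simulation, 20,000 trials per row, each test at 0.05. The homogeneity test has 2 df: Breslow-Day, or Woolf in the row so marked.

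| True pattern | Split per arm | CMH rejects | Homogeneity test rejects |
|---|---|---|---|
| 12.8% vs 8.0% at every site | 225/225/225 | 82% | 5% |
| same | 340/110/225 | 83% | 5% |
| Odds ratios 2.2, 1.0, 0.35 on 8% control | 225/225/225 | 10% | 87% (Woolf) |
| 16%, 10%, 4% vs 10% | 225/225/225 | 5% | 82% |
| same | 340/110/225 | 9% | 87% |
| Odds ratios 2, 1, 0.5 on 10% control | 225/225/225 | 10% | 79% |
| same | 340/110/225 | 31% | 85% |
| 17.6%, 12.8%, 8.0% vs 8.0% | 225/225/225 | 83% | 41% |
| same | 340/110/225 | 92% | 47% |

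Two things follow. With equal sites, CMH rejects about as often under uniform effects (82%) as under moderate heterogeneity with a similar average effect (83%): it responds to the average and not to the spread. How far opposing effects cancel depends on the site sizes, as the 10% and 31% rows show, so the exact rates are illustrative. The mismatch of hypotheses does not depend on them.

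**The case against.** The strongest reply is that this is loose naming and does little harm. Mantel-Haenszel output is often printed with a homogeneity statistic, and the stated purpose suggests that this is the figure the authors meant to read. That is plausible, but the article does not say it. If it is so, the remedy is only to name the statistic.

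Several stronger readings are tempting, and the article does not support them:

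- *The site conclusion will be wrong in both directions.* No rule says how the result will be interpreted, and whether it misleads depends on the true pattern of effects. It can mislead; it need not.
- *The primary analysis is compromised or gated.* Saying that CMH comes first sets an order. Nothing makes the logistic regression conditional on it, and repeating the arm comparison in CMH does no damage while the regression is the analysis named to compare arms.
- *This is the only planned check of consistency.* A condensed article cannot show that. It is the only one named in the article.
- *Consistency across sites is the reason for the trial.* The Background gives several aims, including broader eligibility, priority for patients with HIV, a streamlined intervention and longer follow-up. The stated hypothesis is overall effectiveness.

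Two points against the numbers also stand. The opposing-effect scenarios are extreme: an odds ratio of 0.35 on 8% control means about 3% abstinence at a site offering free medication and counselling, and nothing in the article suggests such a reversal. The replacement test would also miss moderate heterogeneity more often than not.

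The core survives. A method is stated, a purpose is stated, and the method cannot serve the purpose. That is a wrong statement, not detail left to another document.

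**Conclusion.** The point holds as a real but secondary error. As written, CMH is assigned a question that it does not answer. Under the trial's own design effect, identical at all sites, it is significant about 82% of the time against about 5% for a homogeneity test. Under strongly opposing effects the figures are about 10% and 87%. These rates rest on an assumed 225 per arm per site and on assumed patterns of effect, and the opposing pattern is an extreme illustration.

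The primary comparison, its type I error and the sample size of 1,350 stand. What is affected is any statement about agreement between sites that rests on this test.

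**What to change.** Replace the sentence on CMH with:

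*Consistency of the intervention effect across the 3 sites will be assessed by the site-by-arm interaction (2 df likelihood-ratio test) in the logistic model, reported with site-specific effect estimates and 95% CIs.*

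Add that power for moderate heterogeneity is low: about 38% to 47% under assumed Sustained Care rates of 17.6%, 12.8% and 8.0% against 8.0%, depending on the homogeneity statistic and the site split. A non-significant interaction should therefore not be taken as proof of consistency, and the site-specific intervals should carry most of the interpretation. Keep the site-adjusted logistic regression as the primary test. Retain CMH, if at all, only as a supportive site-stratified test of the overall arm effect.

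The cost is one or two sentences and no new data. The article reports follow-up still in progress, so the change could be made before outcomes are analysed, when it cannot look data-driven.

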#### Secondary outcomes

For all outcomes measured at 1, 3, and 6 months, cross-sectional analyses will be used to compare between study groups. Secondarily, a longitudinal analysis using Generalized Estimating Equations (GEE) techniques will be conducted to assess the overall impact of Sustained Care by including data from all follow-up times. Similar to the primary outcome, regression models will be used to compare treatment group adjusting for site and any important confounders; these will be logistic regression for dichotomized outcomes (e.g. self-reported abstinence, any counseling/medication use), and Poisson regression for the number of event outcomes (e.g. number of counseling contacts, number of emergency room visits, number of hospital readmissions). Survival analysis techniques will be used to analyze the duration-related outcome variables (self-reported duration of continuous abstinence and duration of post-discharge medication use). Kaplan-Meier curves will be used to estimate the median duration of tobacco abstinence and medication use. Cox proportional hazard models will examine intervention effects adjusting for potential confounding factors.

*Cost-effectiveness* will be assessed using cost per quit as the main outcome in order to compare our results with other published studies [22,34,35]. The incremental costs per quit are estimated as follows: (Total costs of Sustained Care – Total costs for Standard Care)/(Total successful quits at six months for Sustained Care – Total successful quits at six months for Standard Care) where successful quits are defined according to our primary outcome of 7-day point prevalence abstinence. The major costs tracked in the study are as follows: (1) initial counselor assessment pre-discharge, which includes counselor chart review, counseling, and medication recommendations; (2) Quit Coach medication assessment and cessation support post-discharge; (3) IVR service; and (4) medication costs, including dispensing and delivery. For both study arms, we will track the portion of counseling and medication costs paid for by participants out of pocket and/or by insurance.

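### The primary logistic model adjusts for site but leaves out the five-level stratum used to randomise within site, so the test is slightly conservative if the strata predict abstinence

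*Protocol article*

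**What the plan says.** Under Assignment to treatment group, the protocol article allocates participants at each site "in a 1:1 fashion using permuted blocks of 8". Within site there are five strata: "four strata were created by crossing daily cigarette consumption" (below 10 versus 10 or more a day) with admitting service (cardiac versus non-cardiac), and "a fifth stratum was created for HIV-infected patients". With three sites this makes 5 × 3 = 15 randomisation cells.

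Under Data analysis, Primary outcome, the model is fixed: "Logistic regression analyses will be used to compare the effect of study arm on the primary outcome measure, adjusting for study site". Site is the only covariate named. Under Secondary outcomes, "regression models will be used to compare treatment group adjusting for site and any important confounders"; the stratification factors are not named there either.

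The sample of 1350 is planned for 12.8% against 8.0% validated abstinence, "with 80% power and a 2-tailed type I error rate of .05".

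**The concern.** Blocking within strata makes the arms more alike on the stratification factors than simple randomisation would. If those factors are related to abstinence, the treatment estimate varies less from trial to trial. A model that omits the factors does not see this gain: its standard error is computed as if the arms could differ freely on them. The p-value is then slightly too large and the actual type I error falls slightly below 5%.

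At stake is a small amount of power that the stratified design has already bought. The primary analysis includes one design factor, site, and leaves out the other without explanation. Validity is not at stake, because the error is in the conservative direction.

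**Working it through.** **1. The plan's own figure.** Inputs from Data analysis: p1 = 0.128, p2 = 0.080, d = 0.048, mean p = 0.104, two-sided alpha 0.05 (1.960), 80% power (0.8416).

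Uncorrected n per arm = [1.960·√(2·0.104·0.896) + 0.8416·√(0.128·0.872 + 0.080·0.920)]² / 0.048² = 633.7, rounded up to 634 (1268 in total).

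With continuity correction: n = (633.7/4)·[1 + √(1 + 4/(633.7·0.048))]² = 674.7, rounded up to 675 per arm, or **1350 in total**. The stated figure is reproduced. It makes no use of the strata, so the covariate choice does not change it. At 675 per arm, power without the continuity correction is 82.4%.

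**2. Set-up for the covariate question.** The article does not say how strongly the strata predict abstinence, so this was varied.
- From the article: N = 1350, three sites, five strata per site, blocks of 8, 1:1 allocation, 8.0% against 12.8%, HIV share 4.5% (Trial status).
- Assumed: site shares 50/20/30%; site effects of 0, +0.2 and −0.2 on the log-odds scale; other stratum shares 22% light smokers non-cardiac, 8% light cardiac, 48% heavier non-cardiac, 17.5% heavier cardiac.
- Assumed strength: light smoking and cardiac service each multiply the odds of abstinence by the OR shown, and HIV divides them by it.
- 4,000 simulated trials per scenario. Monte Carlo error is about 0.3 points for type I error, 0.6 points for power and 1% for the SE ratio.

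**3. Results: site-only model against site plus stratum.**

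| OR per factor | Type I error, site only → with stratum | Power, site only → with stratum | Site-only model SE ÷ true SD (under the effect) |
|---|---|---|---|
| 1 | 5.5 → 5.5% | 83.6 → 83.7% | 1.00 |
| 1.5 | 4.9 → 5.1% | 82.9 → 83.3% | 1.00 |
| 2 | 4.5 → 4.8% | 84.5 → 85.2% | 1.02 |
| 3 | 4.2 → 4.7% | 83.2 → 85.0% | 1.04 |
| 5 | 3.9 → 5.1% | 84.2 → 87.4% | 1.05 |

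For ORs up to 3 the SE is overstated by about 0 to 4%, and the power difference is 85.0 − 83.2 = 1.8 points at most. A repeat simulation with its own assumed inputs gave an SE excess of roughly 0 to 2% for ORs of 1.5 to 3, and power of 82.7 → 83.0%, 83.0 → 83.5% and 83.2 → 84.7%.

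**4. What adjustment does to the log-odds interval.** Under the effect, the mean SE of the log OR is 0.184 in the site-only model. With the stratum added it becomes 0.185 (OR 1.5), 0.187 (OR 2) and 0.191 (OR 3), so the interval widens. The estimate also moves away from zero, from 0.527 to 0.565 at OR 3, because the odds ratio is now conditional on stratum. The ratio of estimate to SE goes from 0.527/0.184 = 2.86 to 0.565/0.191 = 2.96. That is where the power gain comes from.

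**5. The risk-difference scale.** For a standardised risk difference (2,500 trials per case), the mean SE falls from 1.651 to 1.642 points (OR 1.5), from 1.653 to 1.631 (OR 2) and from 1.653 to 1.598 (OR 3), or about 0.5%, 1.3% and 3.3%. The true sampling SD at OR 3 is essentially the same in both models (1.59 and 1.585). The precision is already in the design, and the site-only model does not report all of it.

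**The case against.** The strongest reply is that this hardly matters. Up to OR 2 the differences are close to or within simulation error. Site-only power stays above 80% in every scenario, and the error is conservative. The article gives no prognostic strength for any stratum, and it describes HIV as a recruitment priority rather than a predictor of quitting. All of this stands and limits the point to a small refinement.

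Four stronger readings are tempting, and the document does not support them.
- **That the analysis ignores the design.** It does not: randomisation is within site and site is in the model.
- **That the error bars are too wide, as a fact.** This holds only if the strata are prognostic. On the log-odds scale the adjusted interval is wider, not narrower.
- **That the open-ended confounder wording lets covariates be chosen after seeing the data.** That wording concerns secondary models only; the primary set is fixed. Listing secondary covariates is what a condensed article commonly leaves to the analysis plan, which is not shown.
- **That an odds ratio is the wrong measure because the trial was sized on two proportions.** Such sizing does not oblige a risk-difference analysis, and the article does not say that only an odds ratio will be reported.

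The unshown analysis plan may name further covariates. The article, however, states the primary covariate set rather than leaving it open, so the mismatch is in the text as it stands.

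**Conclusion.** The mismatch is real but minor. The primary model names site and leaves out the five-level stratum by which participants are randomised within site. Whether this has any effect depends on how far the strata predict abstinence: none if they do not, rising to about 4% on the standard error and about 2 points of power at an assumed OR of 3 per factor. At OR 5, an extreme case, the figures are about 5% and 3 points. These sizes rest on assumed stratum shares, site shares and ORs; only the direction follows from the design. Type I error is not inflated, and neither the sample size nor the planned power is called into question.

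**What to change.** State the primary model as logistic regression on arm, site and the five-level randomisation stratum (the four combinations of cigarettes per day and admitting service, plus HIV), or give the reason for leaving the stratum out. Note beside it that the resulting odds ratio is conditional on site and stratum, so that nobody expects a narrower interval on that scale. Optionally, report a standardised risk difference from the same model, where the interval does narrow slightly.

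The cost is wording only. The strata are known at randomisation, no new data are needed, and the article reports that follow-up was still in progress, so the change can be made before outcomes are analysed.
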